#### Demographic data

As part of their group therapeutic interventions, The Loss Foundation routinely collects outcome measures and demographic information to evaluate the effectiveness of its services. For the therapy groups, the following data is routinely collected at varying time points across the intervention and securely stored: name; address (for participants requesting paper copies of the intervention manual); age; gender; ethnicity; marital status; highest level qualification; employment; psychological treatment since bereavement; gender of deceased. This data is considered ‘sensitive personal data’ under General Data Protection Regulation (GDPR); however, we believe there is a clear justification to report it as part of the evaluation, given that it will help us to better understand service access, including potential barriers to access.

Bereavement characteristics are also routinely collected by The Loss Foundation including: length of relationship with deceased (years, time since death); relationship with deceased; co-habiting with deceased prior to death; contact with deceased prior to death; frequency of seeing deceased in the three months preceding death; present at the death, death of other loved ones in past three years.

### Sample size

A total of 100 adults bereaved by cancer (50 per arm) will be recruited. As a pilot RCT, the sample size was selected to estimate key feasibility parameters (recruitment, consent, randomisation, adherence, retention, acceptability, and data completeness) with acceptable precision, in line with current guidance on pilot trial sample size determination, rather than to evaluate clinical effectiveness [14, 51, 54]. Although not powered for formal efficacy testing, the sample permits exploration of medium-to-large between-group differences, with any observed outcomes interpreted cautiously to inform outcome selection, variance estimates, and sample size planning for a future definitive RCT.

While online therapeutic groups are often smaller, anticipated attrition and high demand support initial recruitment of 25 participants per group. This size allows structured facilitation, participant engagement, and safety, consistent with prior evidence that slightly larger groups remain effective when appropriately organised [43]. Sessions integrate guided sharing, individual reflection, feedback monitoring, and psychoeducational content, making this format feasible while generating meaningful feasibility data to guide a future definitive RCT.

#### Non-adherence

To mitigate attrition, participants will be contacted regularly throughout the study and informed during consent that they may withdraw at any time. All participants will be screened via telephone to ensure their suitability and understanding of the study. In the event of withdrawal, participants will be followed up with to check on their wellbeing and provided with appropriate signposting support. While some non-response is expected in bereavement research, we will try to minimise missing data by sending reminder emails to prompt completion of follow-up measures.

### Recruitment

The Loss Foundation will send a promotional advert via their mailing list, website, and social media (Facebook and Instagram), inviting individuals to take part in the bereavement therapy groups. Please see Supplementary Material 2: Appendix A for a copy of the advertisement material. Basic information about the study and how to register interest will be displayed on their website and social media accounts. In addition, an email with a link to register interest in the study will be sent to all individuals on their mailing list. An email address for a member of the research team will be provided in these adverts. Participants will self-identify themselves by registering via a secure link and providing their preferred contact details. After self-referral, they will be invited to take part in a screening telephone call with a member of the research team to allow the team to fully explain the trial, to confirm eligibility, and to answer any questions. Following the screening phone call, individuals who give verbal consent for participation and who fulfil the inclusion criteria will be randomised in a 1:1 ratio to either the Non-WL or WL control groups. After randomisation and confirmation of their space in the programme, they will be invited to read the information sheet and sign the electronic consent form to give informed consent prior to participating (please see Supplementary Material 2: Appendix B). The information sheet given to participants includes details on randomisation to start the group immediately (Non-WL) or three months later (WL). Part of the eligibility criteria consists of participants giving informed consent to willingly be randomised including experiencing a delay in the intervention. Participants that do not consent to this will be excluded from the sample. Apart from the initial telephone screening, all correspondence with participants by the research team will be via email, unless the participant requests a telephone call or remote meeting to ask questions.

Participants will be recruited and assessed at baseline from February 2025 with data collection expected to finish in November 2025. Figure 1 shows the CONSORT flow diagram of the study participants.

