### Eligibility criteria

Inclusion criteria are (1) adults (aged 18 or over) who are bereaved by cancer, for example losing a partner, family member, or friend; (2) the time since death must have been more than six months, so as not to interfere with a natural recovery process [48]; (3) self-referral to The Loss Foundation or via a related organisation; (4) have the means to access the therapeutic group online; and (5) participants consent to attending the intervention with the risk of a delay (e.g. by being randomised to the WL group).

Participants will not be eligible if they are (1) adults at high risk to themselves or others in regard to suicide and/or self-harm, (2) significant substance or alcohol misuse which would interfere with participants’ ability to take part in the research, and (3) cannot be involved in other therapy at the same time of the intervention elsewhere. Suicidal risk will be assessed during the telephone screening. Individuals assessed as high risk of harm will be referred immediately to The Loss Foundation’s in-house clinical psychologist for risk assessment and signposting to suitable support services.

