### Comparator

It is possible that people in the WL control group feel frustrated if they must wait for the intervention rather than start immediately. Due to limited resources, The Loss Foundation does not have the capacity to run all the groups simultaneously, which presents a great opportunity to do an RCT given there will naturally be a delay for some starting the intervention. Participants in the WL group who consent for the delay in intervention will be given an electronic version of an information sheet containing signposting to organisations and self-guided information on grief and common signs of wellbeing declining (Please see Supplementary Material 1: Appendix B).

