## Methods: assignment of interventions

### Randomisation and allocation

Following telephone screening and verbal consent, eligible participants will be allocated to groups using a simple randomisation procedure via an online web-based system. Allocation will be communicated to participants by email. Due to the nature of the intervention, neither participants nor facilitators can be blinded to group assignment; however, participants will be asked not to disclose their allocation during outcome assessments. Following allocation, participants will receive an electronic information sheet and consent form, with all further correspondence conducted via email unless otherwise requested. We acknowledge how simple randomisation may result in unequal group sizes or imbalances in baseline characteristics, particularly in smaller samples; these will be examined descriptively and considered when interpreting exploratory outcomes [39].

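### The information sheet and signed consent come after randomisation and the allocation email, so participants who decline once they know their arm can be excluded from the sample

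*Protocol article*

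**What the plan says.** Two sections of the protocol article give the same sequence.

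- **Recruitment.** A telephone call explains the trial and confirms eligibility. Then "individuals who give verbal consent for participation and who fulfil the inclusion criteria will be randomised in a 1:1 ratio". The next step is: "After randomisation and confirmation of their space in the programme, they will be invited to read the information sheet and sign" the electronic form.
- **Randomisation and allocation.** "Allocation will be communicated to participants by email", and "Following allocation, participants will receive an electronic information sheet and consent form".

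Willingness to accept a delay is the fifth inclusion criterion under Eligibility criteria: "participants consent to attending the intervention with the risk of a delay (e.g. by being randomised to the WL group"). Recruitment repeats that informed consent to randomisation, including the delay, belongs to eligibility, and says of those who withhold it: "Participants that do not consent to this will be excluded from the sample".

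The Comparator section recognises that the two arms may react differently: "It is possible that people in the WL control group feel frustrated if they must wait for the intervention rather than start immediately".

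The section headed Analysis population and missing data describes a likelihood-based mixed model under missing-at-random. It does not say who is in the analysis population.

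**The concern.** An eligibility condition that is completed only after the arm is known can depend on the arm. Only WL participants face the delay, so refusal at signature is likelier there. If refusers leave the sample, the groups compared are no longer the groups that were randomised. The mixed model cannot repair this, because a person who leaves before giving any data contributes nothing to the likelihood.

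The primary outcomes of this pilot are feasibility and acceptability. Several of them are percentages of participants set against fixed thresholds that feed the progression decision. Removing early losses from the denominator makes those percentages look better.

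There is a possible further effect on baseline. If T0 is completed after signing, the self-reported starting point of the change-from-baseline comparison is given by people who already know their arm.

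**Working it through.** **Inputs from the protocol.** 100 participants, 50 per arm, 1:1 (Sample size, Recruitment). At least 70% of participants with complete outcome data, at least 70% attending half or more of the sessions, and session adherence of at least 60% (Primary outcomes: feasibility and acceptability). The between-group estimand is the difference in change from baseline over three months (Exploratory secondary analysis).

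**Input not in the protocol.** The number who refuse after allocation. It is assumed here to be 10% to 30% of the WL arm, that is k = 5 to 15.

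**Plan's own figure.** The protocol gives no power or precision calculation to reproduce. Four groups of 25 give 4 × 25 = 100, which agrees with the stated total and is not in dispute.

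**Step 1: order of events.** Set side by side, the two sections give: call and verbal consent, randomisation, allocation email, information sheet and signature. Even if the allocation and the form arrive in one email, the arm is known before signing.

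**Step 2: effect on a completeness rate.** With x participants giving complete data, the rate is x/100 on all randomised and x/(100 − k) on signed consenters.

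| Assumed WL refusals k | x | All randomised | Signed consenters |
|---|---|---|---|
| 5 (10% of 50) | 68 | 68/100 = 68.0% | 68/95 = 71.6% |
| 10 (20% of 50) | 65 | 65/100 = 65.0% | 65/90 = 72.2% |
| 15 (30% of 50) | 60 | 60/100 = 60.0% | 60/85 = 70.6% |

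These cases were chosen to cross 70%. Others do not: 65 complete with 5 refusals gives 65/95 = 68.4%, and 60 complete with 10 refusals gives 60/90 = 66.7%. The fewest exclusions needed to reach 70% are 3 when x = 68 (68/97 = 70.1%), 8 when x = 65 (65/92 = 70.7%) and 15 when x = 60.

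For scale, the 95% half-width of a 70% rate is 1.96 × √(0.7 × 0.3/100) = 9.0 points at n = 100. The shifts in the table are 3.6, 7.2 and 10.6 points.

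**Step 3: the recruitment rate.** Recruitment is judged against a target count, so post-allocation refusals leave it unchanged (if randomised people are counted) or lower it (if signers are counted). They cannot raise it.

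**Step 4: the between-group contrast.** Refusal confined to the WL arm would leave 50 against 45, 40 or 35 by selection. The resulting bias in the group-by-time effect depends on whether refusers would have changed differently, and the documents do not give this.

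**Step 5: baseline, if T0 follows signing.** Suppose knowledge of WL allocation shifts WL scores by b0 at T0 and b3 at three months. The difference in change (immediate minus WL) is then biased by b0 − b3. It is b0 in full if the reaction has gone by three months, and zero if the reaction persists unchanged. In an ANCOVA with baseline slope β it is βb0 − b3.

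**The case against.** Much of the case on the other side stands.

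- **Verbal consent comes first.** It follows a call meant to explain the trial fully and check eligibility, so people have already accepted a possible delay in principle. This should limit refusals. It does not remove the risk, because the written information and the signature still follow allocation.
- **The exclusion sentence can be read as a screening rule.** It follows a sentence about eligibility, and the call is where eligibility is confirmed. A reader might infer that the protocol prescribes removal of people who turn down the WL arm; the wording does not go that far. But it comes after the description of post-randomisation consent and nothing limits it to the period before randomisation, so it permits that removal.
- **The denominators are not shown.** Appendix F, with the progression criteria, is not available, and the article does not say whether the rates use all randomised. The protocol also lists consent and randomisation rates among its metrics, which could reveal the loss. A reader might infer that all feasibility rates are inflated. The text supports only a conditional statement, and recruitment is not among the rates affected.
- **T0 timing is not stated.** The form is to be signed before the person takes part, which suggests that T0 follows, but taking part could mean joining the programme. Table 1 and Figure 1 are not shown.
- **Shifts in level do not carry straight into the estimand.** A reader might assume that decliners lie 0.5 SD above the whole-arm mean and that 10% to 30% decline, and so obtain a shift of 0.06 to 0.21 SD in the remaining WL mean. Such a shift is present at both time points and cancels in a change score unless distress predicts change. It should not be cited as bias in the treatment effect.
- **The clinical comparison is exploratory** and is not meant for confirmatory conclusions. That lowers the stakes for the between-group estimate, but not for the feasibility rates, which are primary.

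**Conclusion.** The concern holds as a risk. The protocol fixes an order in which part of eligibility is completed with the arm known, and its exclusion rule is not confined to the period before randomisation. No section keeps all randomised participants in the sample. Exclusion that depends on allocation is therefore possible and likelier in the WL arm. The documents do not allow its frequency, or the resulting bias in the exploratory comparison, to be computed.

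For the completeness, adherence and acceptability rates, the effect is conditional on signed consenters being the denominator. Under assumed refusals of 5 to 10 WL participants, the worked cases move completeness from 68.0% to 71.6% and from 65.0% to 72.2%, enough to change the result against the 70% threshold. An effect of allocation on baseline scores is a further possibility, resting on the inference that T0 follows signing.

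The documents do not support saying that the randomised comparison is certain to be broken. No stated number in the protocol is wrong on this point.

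**What to change.** 1. In Recruitment and in Randomisation and allocation, set the order as: telephone screen, information sheet, signed e-consent, T0 questionnaires, randomisation, allocation email.
2. State that the exclusion of non-consenters applies only before randomisation.
3. For anyone already enrolled in the present order, use all randomised as the denominator of the post-randomisation feasibility rates, analyse participants as allocated where data exist, and report by arm those who declined after allocation.

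The protocol has recruitment starting in February 2025 and data collection ending in November 2025, so step 3 may be the only part still open. It does not recover clinical data from people who left before T0, but it makes the loss visible and keeps the feasibility rates honest.

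Cost: existing emails and survey links are re-sequenced and a minor amendment is needed. Some people are lost before randomisation instead of after it, and the reported rates may be slightly less favourable.

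### Written informed consent to a possible delay is an eligibility condition but is taken only after allocation, so the exclusion of people who decline can differ between the arms

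*Protocol article*

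**What the plan says.** Eligibility criteria, inclusion item 5, requires that "participants consent to attending the intervention with the risk of a delay".

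Recruitment gives the order of events. A telephone call is held to explain the trial, confirm eligibility and answer questions. Then "individuals who give verbal consent for participation and who fulfil the inclusion criteria will be randomised in a 1:1 ratio". The next step reads: "After randomisation and confirmation of their space in the programme, they will be invited to read the information sheet and sign the electronic consent form". The same section makes informed consent to randomisation, including to a delay, part of eligibility, and adds: "Participants that do not consent to this will be excluded from the sample".

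Randomisation and allocation repeats the order. Allocation is sent by email, and "Following allocation, participants will receive an electronic information sheet and consent form".

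Comparator refers to members of the waitlist group who consent to the delay, and accepts that people in that group may be frustrated at having to wait.

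On the use of the data, the exploratory secondary analysis targets the between-group difference in change over the first three months. The analysis population and missing data section relies on a likelihood-based mixed model under missing at random. Among the primary outcomes, data completeness is acceptable if at least 70% of participants give complete outcome data.

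**The concern.** An eligibility condition should be settled before allocation. Here its written part is settled afterwards. At the screening call everyone faces the same risk of a delay. Once the allocation email has gone out, the delay is certain for one arm and absent for the other, so a refusal at the electronic form can depend on the arm. If those who refuse are then excluded, the arms compared may no longer be the arms that were randomised.

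Two uses of the data are exposed. The first is the exploratory between-group comparison. The second is the set of feasibility figures on which a definitive trial would be planned: if people who drop out on learning their arm are not counted in the sample, retention and data completeness look better than they would in a trial that counts everyone randomised.

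**Working it through.** **Order of events.** Recruitment and Randomisation and allocation agree: screening call and verbal consent, then randomisation, then information sheet and signed consent. Allocation is emailed, and the second section places the form after allocation. The article does not say whether the form comes with the allocation email or later; either way it follows allocation.

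**Which refusals are excluded.** Recruitment uses the term informed consent for the electronic form, and the exclusion sentence follows a few lines later in the same paragraph. Comparator speaks of consent to the delay by people already in the waitlist group. Both favour reading the exclusion as operating after allocation. Signature is also required before taking part, so a non-signer is lost after allocation in any case.

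**Inputs.** From Sample size: "A total of 100 adults bereaved by cancer (50 per arm) will be recruited". No numerical inputs are given for that figure, so it cannot be reproduced and is used here only as the planned size. The 70% completeness mark comes from the primary outcomes section. The refusal rates and the difference between decliners and signers are assumptions; the documents give neither.

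**Shift in the arm contrast.** If a share p of an arm is removed and its mean change differs from that of those who stay by δ SD, the mean of those who stay is off by p × δ. With the same δ in both arms:

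shift = δ × (p waitlist − p immediate)

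| p waitlist | p immediate | Shift at δ = 0.5 SD |
|---|---|---|
| 10% | 0% | 0.5 × 0.10 = 0.05 SD |
| 20% | 4% | 0.5 × 0.16 = 0.08 SD |
| 30% | 4% | 0.5 × 0.26 = 0.13 SD |

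If only the waitlist arm loses people (10%, 20%, 30%, leaving 45, 40, 35), the shift at δ = 0.5 is 0.05, 0.10 and 0.15 SD. Over δ = 0.3 to 0.8 the range is 0.03 to 0.24 SD. At δ = 0.5, a nominal 5% two-sided test would reject in 5.7%, 7.6% and about 10% of trials with no effect.

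**Scale.** At 50 per arm the standard error of a standardised difference is √(2/50) = 0.20, so the 95% half-width is 1.96 × 0.20 = 0.39. The shifts above are smaller than the sampling error.

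**Data completeness.** Suppose 10 of 50 waitlist and 2 of 50 immediate participants do not sign. The sample is 100 − 12 = 88.
- The 70% mark on 88 is 0.70 × 88 = 61.6, so 62 complete sets pass (62/88 = 70.5%).
- The 70% mark on 100 is 70 sets.
- Any count from 62 to 69 therefore passes on the sample and fails on all randomised. For example, 65/88 = 73.9% but 65/100 = 65.0%.

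Within the waitlist arm, 80% completeness among signers is 0.80 × (1 − f) of those randomised, where f is the share declining. That falls below 70% once f exceeds 1 − 0.70/0.80 = 12.5%.

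**Whether the planned analysis repairs it.** It does not. A mixed model under missing at random uses the data of people in the data set; someone excluded from the sample contributes none.

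**The case against.** The strongest reply is that much of the consent process comes before randomisation. The trial is fully explained by telephone, verbal consent is obtained, and accepting the risk of a delay is listed as an inclusion criterion. The exclusion sentence could be read as a screening exclusion. This stands in part: it should keep later refusals few, and a reader who infers that people are randomised without any consent goes too far. It does not remove the second decision point after allocation.

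A reader might also infer that waitlist refusals necessarily disappear from the retention figures. The article does not support that. It defines no retention denominator, it tracks consent and randomisation rates as separate recruitment metrics, and its flow diagram, research protocol and progression criteria are in material not shown. The overstatement is a risk, conditional on the sample being the denominator. Nor does the article show that refusal of the waitlist is the main threat to retention; it says only that frustration is possible.

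Finally, the clinical comparison is exploratory, with a sample size chosen for feasibility parameters "rather than to evaluate clinical effectiveness". That limits the harm to this trial's conclusions, but it does not protect the feasibility figures, which are the primary outcomes.

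**Conclusion.** The concern holds in a limited form. The stated procedure takes written informed consent after allocation and excludes those who do not give it, so an exclusion that differs by arm is possible by design. It can bias the exploratory comparison and, if the sample is the denominator, overstate retention and completeness.

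The size is unknown. The 0.05 to 0.13 SD and the window of 62 to 69 complete sets are illustrations resting on assumed refusal rates and, for the bias, an assumed 0.5 SD difference. They are not estimates for this trial. If nobody declines after allocation, the effect is zero; if people decline equally in both arms and decliners differ from signers equally in both, the contrast does not shift, though the completeness figure still would. The order and the exclusion are certain from the text; the consequences are less so.

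**What to change.** Place the information sheet and signed electronic consent between the screening call and randomisation, and randomise only after signature. Recruitment was to start in February 2025 and data collection to finish in November 2025, so this may come too late here. If so, it should be written into the definitive trial.

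For anyone already randomised under the stated order:
- describe that order as it happened, and say which refusals the exclusion covers;
- use all randomised participants as the denominator for retention and data completeness;
- report post-allocation non-signers by arm in the CONSORT diagram;
- analyse outcomes by allocated arm for everyone who consented to the use of their data, and name post-allocation non-consent as a limitation. People who did not consent can be counted, but their outcomes cannot be analysed.

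The cost is a short wait for the signature before randomisation and, possibly, slightly lower reported retention.
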